## Primary and secondary endpoint

### Primary endpoint

The primary endpoint will be SRQ-20 = or < 7 6 months after enrollment in the trial and/or HSCL-25 <1.06 6 months after enrollment.

We will also collect data on attendance rates to assess feasibility and acceptability throughout the deployment of the intervention:

- Feasibility will be assessed by the percentage of participants completing 1 or more sessions of the intervention and through a focus group with the intervention providers.
- Acceptability will be evaluated using the percentage of participants completing the program (≥50% sessions completed) together with qualitative feedback from participants and providers through a semi-structured interview at the end of the intervention and participants’ feedback from a semi-structured interview at the end of the intervention.

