| **Outcome (s)** | The primary study outcomes will be 1) number of sessions of PM+ attended (acceptance of the program = >50% of sessions attended; feasability within the local context = ≥ 1 session attended and offered and participants’ and providers’ qualitative feedback) and 2) improve their mental health status (overall mental health symptoms by SRQ-20 <7; Hopkins Symtpoms checklist reduction (% of cutoff <1.0.6),  Secondary outcomes: Patient Health Questionnaire (PHQ-9) (0-27; cutoff score, >10) for depressive symptoms; Generalized Anxiety Disorder Scale (GAD-7) score range, 0-21; cutoff score, >10) for generalized anxiety symptoms; Psychlops, psychological outcome profiles (designed to evaluate problem management plus intervention) and World bank toolkit on child-mother relationship. |
| **Study Design** | Randomised control trial |
| **Inclusion/Exclusion Criteria** | All mothers enrolled in Zamcharts clinical trial (n=790) with SRQ-20>7.  Exclusion criteria:   - Mothers who plan to migrate out of the study area within 6 months of the enrolment date - Mothers with severe substance use symptoms, bipolar disorder or squizophrenia - Mothers receiving psychotherapy elsewhere |
| **Measurements and Procedures** | From the total of 265 mothers residing in Lusaka district participating in the ZamCharts study and with mental health needs, we will divide them into two groups:  a control group a intervention group  All women will be called for a screening interview and then, if eligible, invited to receive a baseline interview followed by the intervention (provided in health facilities, by phone and at home) at the beginning and an endline interview at the end of the study.  Families in the intervention group will receive a locally adapted version of the Problem-Management Puls intervention developed by WHO after the baseline interview that allows them to better manage life stressors. The intervention will be provided by trained community health workers, started in groups (1^st^ session) and then continued individually by phone, or in-person at health facilities or at women’s home.  Severe cases will be referred to psychiatry services to evaluate need of antidepressants. |
| **Study Product/Intervention according to KlinV, if applicable** | This study will test an intervention: Problem Management+For Moms (PM+FM) program to reduce mental health symptoms among women and increase mother-child interaction |

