# Study design

We propose to conduct a trial with mothers in Lusaka district. This area was selected to ensure feasibility of the study. Lusaka is an urban area with relatively easy access to care and transportation.

This is a pilot study nested within the “THE IMPACT OF GROWTHCHARTS ON STUNTING AND CAREGIVER AWARENESS: RESEARCH AND POLICY ENGAGEMENT FOR POTENTIAL SCALING (REF. NO. 1411-2020)” clinical trial using a mix-methods analysis. 790 caregiver-child dyads were enrolled in this study in Lusaka in 2021; 30% of these women displayed mild to severe symptoms of depression and/or anxiety (SRQ-20 ≥ 8). For this feasibility study, we will randomly select women from this subgroup. All selected women will be contacted and reassessed with the Self-Reporting Questionnaire (SRQ-20) and further assessed using the Hopkins Symptoms Checklist-25 items^11-13^.

Final ***eligibility*** will be determined by 1) SRQ-20 >7 (clinically significant symptoms of depression or/anxiety anxiety), 2) women with 1 hour a week availability not planning to move within the next 6 months, 3) capacity to consent and 4) not receiving current mental health care. Individuals with active suicidal ideation (determined by Paykel scale^14^), severe substance use (ACOK-SUD >4),^15^ mania or psychotic symptoms^16^ will be excluded and referred to primary care provider or partnering psychiatrist (for emergency cases). We expect that around 70 caregivers will meet the inclusion criteria for the mental health feasibility study. All selected women from the intervention group will be contacted and reassessed with the Self-Reporting Questionnaire (SRQ-20) and the Hopkins Symptoms Checklist 25.

Eligible individuals will continue with a Baseline interview to assess main outcome measures. We plan to focus on engaging participants in each of the research components of the trial (assessments and sessions) through systematic engagement protocol including regular calls to participants and home visits after two weeks of non-responsiveness. All eligible subjects will be randomized with probability of 0.5 to either treatment or control group. Randomization will be based on a random draw generated by the senior author (GF) using the Stata SE 16.0 statistical software package.

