### Secondary endpoints

Secondary endpoints will be the psychological outcome profiles to measure women’s wellbeing and mother-child interaction and child early development.

| **Table 1. Measures and Outcomes** | **Measures Exploratory Efficacy Outcome** |
| --- | --- |
| **Screener measures** | Mania and Psychosis 4 question history (+ MDQ if positive), Capacity to consent (using a validated screening tool), ACOK (> 1 scores for MH and <3 SUD), Paykel suicidality risk scale -.  SRQ-20 >7 |
| **Primary Outcome Measures for EM-PM+ (assessed at enrollment, and 6 months** | |
| **SRQ-20** | 20 items measuring risk of common mental health problem. Used in the intent-to-treat analysis to explore effectiveness of the intervention using control group (endline data from parent study) |
| **Feasibility** | % of 1 or more sessions completed. Completion rates; ease/burden. Qualitative feedback from participants and providers. |
| **Acceptability** | 1) Participation rates; 2) Satisfaction scale; 3) Relevance of PM+FM. Qualitative feedback from participants and providers. |
| **Secondary Outcomes** | |
| **PSYCHLOPS** | Psychological Outcome Profiles (5 items) |
| **WHO-DAS2** | Functionality |
| **HSCL-25** | 10 questions anxiety, 15 depression; (α = 0.90). Used for the pre-post treatment analysis. |
| **World Bank’s** Toolkit **and** Inventory^17^ | Selected measures from the World Bank Toolkit to address mother-child interactions and child early development. |

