## Description of statistical methods

First, we will begin with descriptive analysis of all data by site, using means, variances, quartiles, and graphical assessments of the distribution and skewness of the data. We will describe feasibility and acceptability measures at the participant level.

Then, we will proceed with a pre-post intervention analysis using the Hopkins Symptoms Checklist as a main outcome to compare mental health symptoms before and after receiving the intervention. Moreover, on a second phase, we will calculate effect sizes and trends of effectiveness between intervention group and the non-treated group from the parent trial using endline data from parent trial.

We will use standard linear regression models to assess the impact of the intervention arm on mother’s mental health and mother-child relationship. The intervention outcome variable will be SRQ-20 used as a dichotomous variable with the cutoff at seven. Separate models will be estimated with and without baseline covariates.

The feasibility, acceptability, and difficulties and successes in carrying out research and intervention activities will be explored through a mix-methods analysis including dosage analysis (attendance to the intervention’s sessions) and semi-structured interviews with the participants and focus group with intervention’s providers. The burden of completing the assessments and PM+FM on the time and effort of participants, satisfaction with the intervention, and barriers and facilitators to adherence will be explored through semi-structured interviews with all the participants enrolled in the intervention arm (including participants that have dropped out). Qualitative data resulting from the open-ended questions to participants and focus groups with WCHWs will be transcribed, coded and analysed using a thematic approach to inform on feasibility, acceptability, and explain the potential efficacy of the PM+FM intervention

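### The primary responder definition is not fixed: SRQ-20 and HSCL-25 are joined by an undefined *and/or*, HSCL-25 is primary in some sections and secondary in Table 1, and the SRQ-20 cut-off differs.

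*Protocol*

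**What the plan says.** **Endpoint section (Primary endpoint).** "The primary endpoint will be SRQ-20 = or < 7 6 months after enrollment in the trial and/or HSCL-25 <1.06 6 months after enrollment". It gives no rule for combining the two criteria.

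**Synopsis, Outcome(s).** The mental health part of the primary outcomes reads "overall mental health symptoms by SRQ-20 <7; Hopkins Symtpoms checklist reduction (% of cutoff <1.0.6". Both scales appear, separated by a semicolon. SRQ-20 success is strictly below 7, and the HSCL cut-off is misprinted.

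**Table 1 (Secondary endpoints).** SRQ-20 is the only symptom scale under the primary outcome measures: "Used in the intent-to-treat analysis to explore effectiveness of the intervention using control group (endline data from parent study". HSCL-25 stands under the secondary outcomes: "10 questions anxiety, 15 depression; (α = 0.90). Used for the pre-post treatment analysis".

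**Description of statistical methods.** For the regression model: "The intervention outcome variable will be SRQ-20 used as a dichotomous variable with the cutoff at seven". Before that, the section plans a "pre-post intervention analysis using the Hopkins Symptoms Checklist as a main outcome".

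**Primary Analysis.** The pre-post analysis is named here beside feasibility and acceptability.

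**Study design.** "Final *eligibility* will be determined by 1) SRQ-20 >7". HSCL-25 is administered at screening, but no HSCL-25 threshold appears among the inclusion or exclusion criteria.

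**The concern.** A primary endpoint should give every participant one unambiguous status. Here the status depends on which section is followed. A woman with SRQ-20 of 6 and HSCL-25 above the cut-off is a responder on SRQ-20 alone and under *either*, but not under *both*. A woman with SRQ-20 of exactly 7 is a responder in the endpoint section and a non-responder in the synopsis.

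Under the *either* reading a further oddity arises. Because HSCL-25 is not an entry criterion, a woman could satisfy its half of the endpoint at baseline and be counted as a success without any change.

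What is at stake is the reported responder rate and the freedom to choose among readings after seeing the data. The sample size section says that the preliminary efficacy estimates will be used to size a larger trial, so an unfixed responder rate would carry over into that calculation.

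**Working it through.** **1. The plan's own figure.** The sample size section gives 100 analysed women per arm, power 0.8 for a 20-point difference and 0.9 for 23 points. Alpha is 0.05 (synopsis). Assumed here: two-sided test, control prevalence near 60%.

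Power = Φ[(d√n − z√(2p̄q̄)) / √(p₁q₁ + p₂q₂)]

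- 60% v 40%: (0.20 × 10 − 1.96 × 0.707) / 0.693 = 0.886, so power is 0.81.
- 61.5% v 38.5%: (0.23 × 10 − 1.96 × 0.707) / 0.688 = 1.328, so power is 0.91.

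The stated power reproduces, for one binary outcome. The section calls that outcome prevalence of depression and does not tie it to a combined endpoint.

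**2. How far the reading moves the responder rate.** The documents give neither response rates nor the association between the scales, so these inputs are assumptions. With response rates a and b and phi correlation φ: both = ab + φ√[a(1−a)b(1−b)]; either = a + b − both.

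| Assumed response (SRQ-20, HSCL-25) | Association | Both | Either |
|---|---|---|---|
| 40%, 40% | φ = 0 | 16% | 64% |
| 40%, 40% | φ = 0.5 | 16% + 0.5 × 24% = 28% | 52% |
| 50%, 50% | latent correlation 0.6 | 0.25 + arcsin(0.6)/2π = 35% | 65% |
| 40%, 20% | φ = 0 to 0.5 | 8–18% | 52–42% |

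With similar response on both scales, *both* gives 16–35% and *either* 52–65%.

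**3. Error rate, if two between-arm tests were run.** For two two-sided 5% tests with correlated bivariate normal statistics, the chance that at least one is significant under the null is:

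| Correlation | 0.4 | 0.5 | 0.7 | 0.8 |
|---|---|---|---|---|
| False success | 0.093 | 0.091 | 0.084 | 0.078 |

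Splitting alpha to 0.025 each would give, for 60% v 40% with 100 per arm, (2 − 2.241 × 0.707) / 0.693 = 0.599, so power 0.73. For power 0.80, 118 per arm would be needed.

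**4. The cut-off: below 7 against 7 or less.** Assume endline SRQ-20 roughly normal with mean 6–8 and SD 3.5–4.5. The share scoring exactly 7 is Φ[(7.5−μ)/σ] − Φ[(6.5−μ)/σ], which is 9–11%. That is the shift in response level within an arm.

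The between-arm difference behaves differently. With means of 8 (control) and 6 (intervention) and SD 4:

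- 7 or less: Φ(0.375) − Φ(−0.125) = 64.6% − 45.0% = 19.6 points.
- Below 7: Φ(0.125) − Φ(−0.375) = 55.0% − 35.4% = 19.6 points.

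For 8 v 7 or 7 v 6 (SD 3.5–4.5) the two rules differ by less than 0.5 points. Over whole-number means from 5 to 9 they differ by at most 1.7 points.

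**5. Which cut-off fits the rest.** Entry is SRQ-20 above 7, and the protocol describes symptomatic women as scoring 8 or more. Only 7 or less is the complement of these.

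**The case against.** The strongest reply is that the analysis text already separates the scales. Study design, Table 1 and the statistical methods give HSCL-25 to the pre-post analysis and SRQ-20 to the intention-to-treat comparison with controls. On that view the calling of HSCL-25 a main outcome concerns the pre-post analysis only and agrees with its entry in Table 1. This stands: the phrase is not a separate contradiction of Table 1. It does not rescue the endpoint section and the synopsis, which still make HSCL-25 primary, nor the Primary Analysis section, which places the pre-post analysis there.

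It can also be said that *and/or* simply means *either*. That reading would settle the rule but would conflict with Table 1 and with the model, which use SRQ-20 alone.

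Three stronger conclusions are tempting and are not supported:

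- **That the plan has an 8–9% error rate.** The sample size section says efficacy will only be explored to obtain preliminary estimates, no success rule is stated, and no second between-arm test on HSCL-25 is planned. The figure applies only if such tests were run and a success claimed on either.
- **That the cut-off conflict is worth half of the 20-point target.** The 9–11% is a shift in response level; the 20 points are a difference between arms. Both arms shift together, and the difference hardly moves.
- **That the combined endpoint cannot be computed between arms.** The documents describe no endline HSCL-25 collection in controls, but they do not rule it out either.

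Finally, the cut-off conflict is one synopsis entry against consistent wording elsewhere, so it is a correction rather than a real analytic choice. That also stands.

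**Conclusion.** The point holds as a defect in the definition of the primary endpoint. The combining rule is missing, and HSCL-25 is primary in the endpoint section and synopsis but secondary in Table 1. Following the protocol as written therefore does not determine the primary responder rate. Under assumed response of 40–50% on each scale (φ of 0 to 0.5, or latent correlation 0.6), the readings range from 16–35% to 52–65%. The rates and associations are assumptions, since the documents give none. That a woman could meet the *either* version at baseline is a logical possibility; the documents do not allow it to be sized.

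The 8–9% false-success rate (correlation 0.4–0.8) is conditional as described. The SRQ-20 cut-off conflict alters the status of women scoring exactly 7 and the response level in each arm, with little effect on the treatment contrast. The exploratory label lowers the weight of the error-rate argument but does not remove the contradiction, because the estimates are meant to size a later trial.

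**What to change.** 1. **Primary endpoint section:** name one primary efficacy endpoint, the between-arm comparison of the proportion with SRQ-20 of 7 or less at 6 months. This is the complement of the entry rule and fits the dichotomised SRQ-20 already named for the regression. Stating the dichotomy explicitly also settles whether the score or the proportion is primary. Delete the *and/or* HSCL-25 criterion.
2. **Synopsis, Outcome(s):** remove the HSCL criterion from the primary outcomes and change the SRQ-20 rule from below 7 to 7 or less.
3. **Description of statistical methods:** say that a score of 7 counts as a response.
4. **Table 1:** keep HSCL-25 as secondary.
5. **Description of statistical methods and Primary Analysis:** label the HSCL-25 pre-post analysis as secondary or supportive.

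The cost is protocol wording only. No visit, instrument or sample size changes, and the stated power for one binary outcome is kept. The wording should be settled before endline data are seen.

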### Secondary endpoints

Secondary endpoints will be the psychological outcome profiles to measure women’s wellbeing and mother-child interaction and child early development.

| **Table 1. Measures and Outcomes** | **Measures Exploratory Efficacy Outcome** |
| --- | --- |
| **Screener measures** | Mania and Psychosis 4 question history (+ MDQ if positive), Capacity to consent (using a validated screening tool), ACOK (> 1 scores for MH and <3 SUD), Paykel suicidality risk scale -.  SRQ-20 >7 |
| **Primary Outcome Measures for EM-PM+ (assessed at enrollment, and 6 months** | |
| **SRQ-20** | 20 items measuring risk of common mental health problem. Used in the intent-to-treat analysis to explore effectiveness of the intervention using control group (endline data from parent study) |
| **Feasibility** | % of 1 or more sessions completed. Completion rates; ease/burden. Qualitative feedback from participants and providers. |
| **Acceptability** | 1) Participation rates; 2) Satisfaction scale; 3) Relevance of PM+FM. Qualitative feedback from participants and providers. |
| **Secondary Outcomes** | |
| **PSYCHLOPS** | Psychological Outcome Profiles (5 items) |
| **WHO-DAS2** | Functionality |
| **HSCL-25** | 10 questions anxiety, 15 depression; (α = 0.90). Used for the pre-post treatment analysis. |
| **World Bank’s** Toolkit **and** Inventory^17^ | Selected measures from the World Bank Toolkit to address mother-child interactions and child early development. |

## Measures to minimize bias

This study will be conducted as a randomized controlled trial, which should minimize the risk of selection and confounding bias. Women’s wellbeing will be assessed objectively through trained interviewers blinded by the treatment condition minimizing the risk of reporting or social desirability biases.

## Study duration and duration of participant’s participation

The project will be divided into three phases: A preparatory phase (Month 1 - 6) will primarily focus on developing and adjusting the intervention, and for piloting field logistics. This initial phase will be followed by a trial phase (Month 7-12) and a final analysis and dissemination phase (year 2).

We anticipate to start identification cases, screening and enrollment to the trial in October- Nov. 2022. An Endline assessment will be conducted approximately 5 months after completion of the baseline survey (April 2022).

### Schedule of events

Table 1. Project Milestone

| Date | Description |
| --- | --- |
| July 2022 – Sept. 2022 | Study setup, IRB approval, identification of WHW, |
| Sept. 2022 – Oct. 2022 | Training of 4-6 WCW. Identification of participants (Screening) |
| Nov. 2022 – Mar 2023 | Baseline and Intervention period |
| May 2023 - June 2023 | Endline assessments |
| Jul 2023 – Sept. 2023 | Data analysis |
| Oct. 2023 – Dec. 2023 | Study dissemination |

## Early termination of the study

We do not foresee any events that would result in an early termination of the study.

# Selection of the study participants

## Study setting

This study will be conducted in Lusaka district of Zambia

## Recruitment

All women participating in Zambcharts parent study complying with the inclusion criteria and living in the enumeration areas (each enumeration area contains 200-500 households, and correspond to villages in rural settings and blocks in urban areas) of Lusaka district will be invited to participate in our study. Participants will be contacted by trained study staff, who will explain the study to caregivers and enroll them into the study conditional on their consent.

We plan to focus on engaging participants in each of the research components of the trial (assessments and sessions) through systematic engagement protocol including regular calls to participants and home visits after two weeks of non-responsiveness.

## Inclusion criteria

1) SRQ-20 >7 (clinically significant symptoms of depression or/anxiety anxiety), 2) women with 1 hour a week availability not planning to move within the next 6 months, 3) capacity to consent and 4) not receiving current mental health care.

## Exclusion criteria

Women with active suicidal ideation (determined by Paykel scale^14^), severe substance use (ACOK-SUD >4),^15^ mania or psychotic symptoms^16^ will be excluded and referred to primary care provider or partnering psychiatrist (for emergency cases). Additionally, women planning to move in the next 6 months were excluded from the study.

We expect that around 70 caregivers will meet the inclusion criteria for the mental health feasibility study.

All eligible subjects will be randomized with probability of 0.5 to either treatment or control group. Randomization will be based on a random draw generated by the senior author (GF) using the Stata SE 16.0 statistical software package.

## Criteria for discontinuation of study

We do not foresee any circumstances under which the trial would be discontinued.

### Discontinuation of individual participants

It is possible that some caregivers will not want to (consent to) participate in the endline survey. Based on previous studies in this area, we believe this risk to be small. We have allowed for 15% attrition (mostly due to migration) between the baseline and endline survey.

1. **Treatment of participants**

## Identity of investigational products

### Experimental intervention (treatment / medical device)

To develop the PM+FM intervention, we followed the Castro-Barrera framework for cultural adaptation of evidence-based interventions. ^23^ Therefore, the intervention is culturally adapted to women’s local context of social and cultural values and norms.

This study aims at assessing one intervention: Problem Management Program-For Moms

**Intervention:** The PM+FM intervention is a cognitive-behavioral therapy-based transdiagnostic psychosocial intervention using a context-adapted version of the PM+ manual from WHO and specific sections from the Strong Minds psychosocial intervention and psychoeducation material from a psychosocial stimulation intervention in early childhood to improve women’s wellbeing including mental health symptoms and mother-child relationship. The intervention:

- Is provided individually, organized in 10 to 12 1-hour sessions and provided on a weekly basis by a specifically trained and supervised WCW in women’s homes.
- Lasts a maximum of 5 months. Following regular clinical patterns of attendance, participants can schedule the sessions within this period to finish the program.
- Will be culturally adapted to women’s local context of social and cultural values and norms using a systematic cultural adaptation framework. To develop the PM+FM intervention, we followed the Castro-Barrera framework for cultural adaptation of evidence-based interventions.^18^ Therefore, the intervention is culturally adapted to women’s local context of social and cultural values and norms.
- Follows a collaborative and patient-centered approach where individual’s needs are central and contents of the intervention are adapted to each person.
- Combines psychoeducation, problem-solving and cognitive restructuring techniques, motivational interviewing approach, effective communication practice and mindfulness practice.

| **PM+FM Intervention summary of contents** | |
| --- | --- |
| Session 1 | Symptom’s assessment. Introduction of the program and confidentiality. Cultural Formulation interview to understand woman’s need. Psychoeducation about mental health needs (understanding adversity) and maternal-child positive relationship. Relaxing breathing. |
| Session 2 | Barriers to change, managing problems and stress management strategies. Introduction to mindfulness. |
| Session 3 | Symptom’s assessment. Managing Problems (Problem-solving technique), “get going, keep doing” strategies (Behavioral activation). Managing Stress strategy and mindfulness practice. |
| Session 4 | Managing Problems: understanding unhelpful thoughts. Positive upbringing strategies. Stress management and mindfulness practice. |
| Session 5 | Symptom’s assessment. Importance of support for positive upbringing and stress management. Strengthening social support. Mindfulness practice. |
| Session 6 | Effective communication skills, Mindfulness practice |
| Session 7 | Symptoms’ assessment. Improving healthy habits for me and my child (nutrition, sleep, and substance use). Mindfulness practice. |
| Session 8 | Positive thinking and self-compassion practice. Mindfulness practice. |
| Session 9 | Review of the techniques. Staying Well and Looking to the future (Self-care plan). Mindfulness practice. |
| Session 10 | Review of self-care plan. Social resources and referral. Mindfulness practice. Closure and Ending the programme. |

- 2 booster sessions can be delivered to accommodate urgent needs and/or consolidate core content of the program (i.e. problem management and self-care plan).
- **Management of Severe cases:** Cases found to be severe in mental health symptoms or substance use symptoms, will be referred to our collaborating team of psychiatrists and psychologists from UTH in Lusaka, lead by [name]. Medication prescription and monitoring will be tracked by the research team. Pharmacological treatment (indicated by the psychiatrist) will be subsidized by the project in case participant cannot afford it.
- **Training and Supervision of WHW:** We will identify 4 to 6 people with at least a high school diploma, with some previous experience of working within the community and interested in mental health topics to be trained as WCWs. The training program occur in 4 full days of instruction followed by 4 weeks of role-plays with 2 hours weekly group supervision. Instructional training starts by addressing program objectives, ethics, emergency protocol procedures, psychoeducation about common mental health problems (day 1) and basic components of psychotherapy (i.e. motivational interviewing, cultural formulation, mindfulness practice and problem solving technique (Day 2). During the third and fourth day of instructional training, we will focus on the specific sessions’ content, special clinical situations (i.e. substance use involvement, domestic violence, and suicidal thoughts), and training related to their integration in the clinical site, including communication and referral procedures. It will end with a review of the emergency protocol procedures. Instructional trainings will be videotaped for further use for needed subsequent trainings. After roleplaying with two example cases and receiving weekly supervision. WCWs will deliver the intervention to two first cases as pilots. Pilot cases (ineligible for the trial because of mild symptoms or because already receiving treatment). All role-plays and pilot sessions will be audiotaped, transcribed and heard by the supervisor. The **supervision protocol** includes weekly individual and group supervision throughout the training process (individual supervision) and trial (group supervision) to support the WCWs and provide feedback on the session tapes, share the fidelity forms and to resolve issues related to the delivery (e.g. severe cases and drifting). We plan to collect data on training needs and mental health basic knowledge among the WCWs at the moment of hiring and every 6 months to evaluate mental health care delivery capacity. The supervisor will be a local psychologist specially trained by the PI of this project.

